### The control group

Participants in the control group will receive a 51-page education book whose content is the same as Part 1 of the intervention workbook. It includes SM strategies after cancer treatment but excludes SM skill training. At the end of the study, the control group can request the intervention.

### Study outcomes

The overview of the psychometric properties of primary and secondary outcome measures is presented in Table 4.

**Table 4 Tab4:** EMPOWER study outcomes

Outcome	Measurement used	Measurement description	Psychometric properties
**Primary outcome**			
Empowerment	Empowerment Scale for Women with Breast Cancer	30 items and 3 factors. Factors include ‘intrapersonal factor’ (14 items), ‘interactional factor’ (8 items), and ‘behavioral factor’ (8 items). 5-point Likert scale. High score indicates higher empowerment.	Goodness of fit of the final research model was very appropriate as shown by χ^2^/df = 1.86, TLI = 0.90, CFI = 0.92, SRMR = 0.06, and RMSEA = 0.05. Criterion validity was evaluated by total correlation with the Cancer Empowerment Questionnaire 0.78. Cronbach’s alpha for total items was 0.93, and test-retest reliability was 0.69 [29].
**Secondary outcomes**			
Self-efficacy	Korean version of the Cancer Survivors’ Self-Efficacy Scale	10 items and 2 factors. Factors include ‘Self-efficacy for managing health problems’ (5 items) and ‘self-efficacy for seeking help and support’ (5 items). 10-point Likert scale. Higher score indicates higher self-efficacy.	Construct validity was evaluated with general self-efficacy (0.511), anxiety (−0.596), depression (− 0.554) and health-related quality of life (0.586). Cronbach’s alpha of total scale and subscales was 0.86–0.92 [30].
mental adjustment	The Mini-Mental Adjustment to Cancer	29 item and 4 factors. Factors include Helpless-Hopeless (HH), Anxious Preoccupation (AP) Positive Attitude (PA), Cognitive Avoidance (CA), and Fighting Spirit (FS).	Construct validity was evaluated with each of anxiety and depression subscales of HADS, AP (0.63, and 0.58), HH (0.54, and 0.59), FS (−0.30, and − 0.37), and PA (− 0.19, and − 0.23). Cronbach’s alpha was 0.50–0.86 and test–retest reliability was 0.68–0.88 [32].
Anxiety and depression	Hospital Anxiety and Depression Scale	14 item and 2 subscales. Subscales are ‘an anxiety (HADS-A)’ and ‘a depression (HADS-D)’. 4-point Likert scale. Higher score indicates greater anxiety or depression.	Construct validity of HADS-D was evaluated with Beck Depression Inventory 0.80, and HADS-A with Self-Rating Anxiety Scale was 0.79. Items of the HADS-A and corrected item total score was 0.55 and HADS-D was 0.47. Cronbach’s alpha for total items was 0.89 and 0.86 [35].
HRQOL	36-Item Short-Form Survey	36 items, 8 subscales and 2 domains. Domains include ‘physical component’ and ‘mental component’. Each subscale is scored 0 to 100. Higher score indicates better functioning and well-being.	The SF-36 has been validated in South Korea. Cronbach’s alpha was 0.89 for physical component, 0.87 for mental component, and 0.93 for total score [37].

*CFI* comparative fit index, *HRQOL* health-related quality of life, *RMSEA* root mean square error of approximation, *SRMR* standardized root mean square residual, *TLI* Tucker-Lewis Index

### Primary outcome

We will evaluate empowerment using the Empowerment Scale for Women with Breast Cancer [29]—a 30-item self-report instrument consisting of intrapersonal factors (14 items), interactional factors (8 items), and behavioral factors (8 items). Scored on a 5-point Likert scale, a high score indicates higher empowerment. The scale has shown good validity and reliability [29].

### Secondary outcomes

We will measure self-efficacy for SM among BCS using a Korean version of the Cancer Survivors’ Self-Efficacy Scale (CSSES-K) [30]. The original version of CSSES is an 11-item questionnaire assessing cancer survivors’ cancer-related self-efficacy [31]. The CSSES-K is a 10-item, 2-factor questionnaire. The factors are ‘self-efficacy for managing health problems’ (5 items) and ‘self-efficacy for seeking help and support’ (5 items) [30]. Each item is rated on a 10-point scale from 1 (not at all confident) to 10 (totally confident); a higher score indicates higher self-efficacy. The original version of CSSES has a good reliability and validity [31], thus the CSSES-K has adequate internal consistency (Cronbach’s alpha = 0.86–0.92) [30].

We will evaluate mental adjustment using a Korean version of Mini-Mental Adjustment to Cancer (Mini-MAC) [32]. The original Mini-MAC is a 29-item self-rating questionnaire and includes 5 factors: 4 for Fighting Spirit (FS), 8 for Help-Hopeless (HH), 8 for Anxious Preoccupation (AP), 5 for Fatalism (FA), and 4 for Cognitive Avoidance (CA) [33]. The Korean version of Mini-MAC uses a 4-point Likert scale and includes 4 factors—8 items for HH, 8 for AP, 4 for CA, and 9 for Positive Attitude (PA). The Cronbach’s alpha coefficients of the Korean version of Mini-MAC are 0.50–0.86, and test-retest coefficients are 0.68–0.88 [32].

Anxiety and depression will be assessed using the Hospital Anxiety and Depression Scale (HADS) [34]. HADS is a 14-item self-report instrument assessing symptoms of anxiety and depression that reflects 2 subscales, with 7 items for depression and 7 items for anxiety. Each item is scored from 0 to 3, with higher scores indicating more distress. The Korean HADS has been validated and has shown good validity and reliability [35].

We will measure HRQOL using the 36-item Short-Form Health Survey (SF-36) [36]—a 36-item questionnaire that consists of 2 domains (physical and mental) and 8 subscales (functioning, physical role functioning, bodily pain, general health, vitality, social role functioning, emotional role functioning, and mental health). Each subscale is scored from 0 to 100, with higher scores indicating better functioning and well-being. The SF-36 has been translated into Korean and shown good validity and reliability [37].

### Sample size calculation

Based on the primary outcome ‘empowerment’, at least 78 patients will be required using an effect size of 0.65 [38], a power of 0.8, and an alpha less than 0.05. Assuming an estimated dropout of 20%, 47 participants will be needed in each group (a total of 94 participants).

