**Methods:**

The conceptual framework of this study is the Chronic Care Model, which posits that SMS can influence patient-provider relationships and ultimately improve health outcomes. We will conduct a multi-center, 2-armed randomized controlled trial to assess the effectiveness of EMPOWER among post-treatment breast cancer survivors in South Korea. The trial will include 94 women who completed primary breast cancer treatment within the last 6 months. Participants will be randomly assigned to the intervention group or the wait-list control group (1:1). The intervention group will receive a 7-week partnership-based and needs-tailored SMS intervention via telephone counseling. The primary outcome is empowerment. The secondary outcomes include self-efficacy for post-treatment self-management behaviors, mental adjustment, psychological distress, and health-related quality of life (HRQOL). Data will be collected by self-reported questionnaire at baseline, post-intervention, and 3-month follow-up.

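### The 20% dropout allowance is too small: 94 women less 20% leaves about 75, below the 78 the protocol says it needs

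*Protocol article*

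**What the plan says.** Under Sample size calculation, the protocol article states that "at least 78 patients will be required using an effect size of 0.65 [38], a power of 0.8, and an alpha less than 0.05". The next sentence adds the allowance for loss: "Assuming an estimated dropout of 20%, 47 participants will be needed in each group (a total of 94 participants". The Methods part of the abstract repeats the total: "The trial will include 94 women who completed primary breast cancer treatment within the last 6 months".

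The article does not print the inflation formula, the test behind the 78, or whether alpha is one-sided or two-sided. Allocation is 1:1 (Randomization section).

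**The concern.** A dropout allowance exists so that the required number of patients is still there after the expected loss. Here it does not do that: taking the assumed 20% away from the planned 94 leaves fewer than the 78 stated one sentence earlier. The pattern fits a common slip, in which the required number is raised by the dropout percentage instead of being divided by the proportion expected to remain.

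At stake is the consistency of a core design statement. Required number, dropout rate, total and power are given as one set, but at the stated dropout the total gives neither the required number nor, on the calculation that produces 78, the stated power. The wrong figure is also likely to be carried into the results report.

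**Working it through.** **Inputs, all from Sample size calculation unless noted**

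- Standardised effect size 0.65, power 0.80, alpha 0.05
- Required number: 78 in total, so 39 per arm at 1:1 (Randomization)
- Dropout: 20%
- Planned number: 47 per arm, 94 in total
- Assumed here: two-sided alpha and a two-sample t-test. The article states neither, but together they reproduce the 78.

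**Step 1. Reproduce the 78.** With n per arm, the t-test has 2n − 2 degrees of freedom and noncentrality 0.65 × √(n/2). Solving for power 0.80 gives n = 38.14, rounded up to 39 per arm, 78 in total. Power is 0.799 at 38/38 and 0.809 at 39/39. A one-sided test would need 30 per arm, 60 in total, which does not match. The stated base is therefore right under the two-sided reading.

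**Step 2. Reproduce the 94.** Two ways of allowing for 20% loss:

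| Method | Per arm | Total |
|---|---|---|
| Multiply by 1 + 0.20 | 39 × 1.2 = 46.8 → 47 | 78 × 1.2 = 93.6 → 94 |
| Divide by 1 − 0.20 | 39 / 0.8 = 48.75 → 49 | 78 / 0.8 = 97.5 → 98 |

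The first row gives the printed figures exactly. Only the second keeps 78 women after a 20% loss: 98 × 0.8 = 78.4.

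**Step 3. What 94 delivers.**

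- Completers at 20% loss: 94 × 0.8 = 75.2 (37.6 per arm), against 78 required
- Largest dropout that still leaves 78: 1 − 78/94 = 0.170, or 17.0%

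**Step 4. Power at d = 0.65, two-sided 0.05, completers only.**

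| Completers per arm | Power |
|---|---|
| 39 / 39 | 0.809 |
| 38 / 38 | 0.799 |
| 38 / 37 | 0.793 |
| 37 / 37 | 0.788 |

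**Step 5. Could 94 come from another route?** The normal approximation gives 2 × ((1.960 + 0.842) / 0.65)² = 37.15 per arm before rounding, and 37.15 / 0.8 = 46.4, which also rounds up to 47. But that base is 38 per arm, 76 in total, when rounded, and so disagrees with the printed 78. Alternatively, the 20% could be meant as a share of the 78 completers. The 94 − 78 = 16 extra women are then 16/94 = 17% of those randomized, which is not what a 20% dropout ordinarily means. On either route the paragraph still needs correcting.

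**The case against.** The strongest objection is that almost nothing is lost. Against the 0.80 target, 0.793 is a shortfall of 0.7 percentage points; part of the wider gap from 0.809 comes from rounding 38.14 up to 39. With 38 and 37 completers, the effect detectable at 80% power is 0.656 instead of 0.65.

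Further, the power figures describe a completers-only t-test, whereas the Statistical analysis section plans linear mixed models under a missing-at-random assumption with intention to treat. A woman lost after the 8-week assessment still contributes data, and using the baseline value raises power. The article gives no baseline-to-follow-up correlation, so a range has to be assumed. With 38/37 completers and baseline adjustment, power is about 0.797 at r = 0.1, 0.809 at 0.2, 0.829 at 0.3 and 0.894 at 0.5. A correlation of about 0.2 would make good the loss. The test-retest reliability of 0.69 in Table 4 is a different quantity, but it suggests that a correlation above 0.2 is plausible.

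Much of this stands. The effect on power is minor, and the planned analysis may well reach 0.80. The multiplication by 1.2 is also inferred, not printed. None of it removes the contradiction. The sample size paragraph names a minimum number of patients and an allowance meant to protect it; it does not mention repeated measures or a baseline correlation as a reason for accepting fewer. The count of 75 against 78 needs no assumption about test or model.

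**Conclusion.** The concern holds. The protocol's own figures leave 75.2 women where it requires at least 78, and nothing elsewhere in the article corrects this. The matching total is 98, four more than planned; alternatively, the dropout that 94 can absorb is 17.0%, not 20%.

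The shortfall in numbers rests only on the printed figures. The power of about 0.79 (0.793 at 38/37, 0.788 at 37/37) rests also on a two-sided two-sample t-test in completers without baseline adjustment; it is not a forecast of power under the mixed model. This is a small but definite error in the sample size statement. It does not threaten the trial's conclusions, but it should be corrected.

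**What to change.** Correct the Sample size calculation paragraph in one of two ways.

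1. Keep 94 and restate what it delivers: 94 randomized gives 78 evaluable women if dropout is at most 17%; at 20% dropout about 75 remain, and power is about 0.79 for an effect size of 0.65 at two-sided alpha 0.05. The text should name the two-sample t-test and the two-sided alpha as the basis, since the article states neither. This costs nothing except a slightly less favourable power figure.
2. Keep 20% dropout and 78 evaluable, and change the total to 98 (49 per arm), here and in the abstract. This costs four more participants.

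The first is enough if recruitment is already fixed at 94.

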### Statistical analysis

We will describe the characteristics of the study participants using frequency and percentage for categorical variables and means and standard deviations for continuous variables. To compare baseline characteristics between the two groups, we will use independent *t*-tests for normally distributed continuous variables, the Mann-Whitney test for non-parametric variables, and the chi square test for categorical variables. We will use linear mixed models to analyze the efficacy of EMPOWER and Cohen’s d to estimate effect size as large (≥0.80), moderate (0.5–0.79), or small (< 0.50) [39]. Missing data will be handled under the missing-at-random assumption. We will perform all analyses using IBM SPSS Statistics version 25.0 (IBM, Armonk, NY, USA) according to the intention-to-treat principle and consider a *p*-value < 0.05 significant.

## Discussion

We developed the EMPOWER intervention with the intention of improving health outcomes by enhancing empowerment and increasing self-efficacy in post-treatment BCS, thus facilitating successful transition from hospital-based survivorship care to SMS care. Expected outcomes include decreased psychological distress, better mental adjustment, and improved HRQOL. If successful, this study will provide evidence that SMS may be an important survivorship care model.

EMPOWER has several strengths. First, it is theory-based; we applied self-efficacy theory [27], Lorig and Holman’s model [22], and motivational interviewing technique [28] for development and delivery of the intervention. EMPOWER’s main mechanism will be to facilitate partnership between provider and participant and increase self-efficacy of the participant. Second, EMPOWER is needs-tailored. Although substantial BCS have unmet needs after cancer treatment [40, 41], there is a lack of interventions that meet their supportive care needs in a personalized manner. We believe that EMPOWER’s Part 2 intervention (4-week SM skill training for participant’s chosen topic) will work as a needs-based tailored intervention. Third, EMPOWER’s SM skill training protocol is evidence-based. We developed action-planning protocols for each SM topic based on interventions that were already proven effective.

EMPOWER has also several weaknesses. First, it can be resource intensive because it is delivered by a well-trained nurse via telephone. That burden could be reduced, however, by delivering the Part 1 intervention (SM education) by an app or on the web. Second, SM skill training is available for only 6 topics (management of pain, fatigue, insomnia, distress, exercise, and diet). As more evidence becomes available, other SM topics could be developed. Third, generalization to a wider setting and in other countries must be done with caution because the prioritized SM topics were chosen by the Korean population.

## Conclusion

EMPOWER is a theory-based SMS intervention unique in its provider-partnership and needs-tailored approach. If found successful, the EMPOWER trial will offer insights into how clinicians can engage in chronic care for BCS after treatment using SMS intervention.

## Data Availability

Not applicable.

## Abbreviations

BCS: breast cancer survivors
CCM: Chronic Care Model
CSSES-K: Korean version of the Cancer Survivors’ Self-Efficacy Scale
EMR: Electronic medical record
HADS: Hospital Anxiety and Depression Scale
HRQOL: Health-related quality of life
Mini-MAC: Mini-Mental Adjustment to Cancer
RCT: Randomized controlled trial
SF-36: 36-item Short-Form Health Survey
SM: Self-management
SMS: Self-management support
SPIRIT: Standard protocol Items: Recommendations for Interventional Trials
